| --- |
| **5. Objectives of the study:**  **5.1 General objective** (overall objective, one paragraph maximum)  To identify the appropriate drug which can be used for treating *P. falciparum* sub-patent parasitaemia and gametocyte reservoir during the dry season in an area of marked seasonal malaria transmission in eastern Sudan. The ultimate aim is to reduce malaria morbidity and mortality during the transmission season.  **5.2 Specific objectives:** (should cover the details of the general objective)   - To identify individuals with sub-patent parasitaemia during the dry season using nested PCR technique - To identify gametocyte carriers among them using RT-PCR - To carry out a community-based intervention study for testing the efficiency of two drug combinations; Artesunate plus Sulphadoxine Pyrimethamine (S/P) and Artesunate plus Sulphadoxine Pyrimethamine (S/P) plus primaquine in clearing sub-patent parasitaemia and gametocytaemia from carriers at the end of the dry season. - To evaluate the effect of such a strategy on malaria morbidity and mortality during the transmission season.   **5.3 Secondary objectives (optional):** these are subsidiary objectives that could be studied during the course of the project but are not the main objectives of the study.  None |
| **6. Materials and Methods** (that could best achieve the study objectives)  **6.1 Study area/setting** (description of the area or setting where the study will be conducted)  The study will be carried out in two villages in eastern Sudan. These villages have relatively stable conditions and no modifications in the applied control measures are expected. They are far from each other and matched for malaria burden, environmental factors and control measures.  The whole area is characterized by seasonal malaria transmission. The season is confined to three months of the year, October – December. The main malaria parasite is *P. falciparum* and the main mosquito vector is *Anopheles arabiensis*10. Subpatent parasitaemias persist in some individuals throughout the dry season, with re-appearance of clinical symptoms in the malaria season associated with reinfection11.  **6.2 Study subjects** (eligibility and exclusion criteria for the study subjects)  The whole residents of the two villages will be recruited into the study. The following ones will be excluded from drug testing :   - pregnant women - children < 3 year old - history of allergy to sulpha drugs - infection with *Plasmodium* species other than *falciparum*   6.3 Combination Therapy:  The antimalarial drug combinations would be: Artesunate (AS) + Sulphadoxine Pyrimethamine (S/P) + primaquine (single dose of 0.75 mg of base/kg body weight) for one group and AS + S/P for the other. These are intended to treat malaria cases, sub-patent parasitaemia and gametocyte carriage. AS and S/P are blood schizontocidal drugs active against *P. falciparum* and gametocytocidal against developing gametocytes of *P. falciparum*. The addition of premaquine is expected to clear mature gametocytes.    6.4 Study design  A community-based intervention study will be conducted in the two villages. The study will start by a baseline evaluation of malaria morbidity and mortality during the transmission season of 2003.  A cross-sectional clinical, parasitological and molecular survey will be carried out during the dry season of 2004. Villagers will be screened for malaria parasite by microscopy. Samples detected negatives by blood films will be screened by conventional nested PCR *Pfs25* primers for detection of sub-patent parasiteamia. Blood will be collected from individuals detected positive by PCR for detection of gametocyte using the RT-PCR technique.  A treatment trial will then be carried out on malaria cases and asymptomatic carriers at the end of the dry season to test the efficacy of two combinations of antimalarial drugs.They will be followedup on days 3, 7 and 14 to confirm the clearance of *P. falciparum*  sub-patent parasitaemia and gametocyte carriage.  The impact of treating sub-patent parasitaemia and gametocyte reservoir on malaria morbidity and mortality will then be evaluated by carrying out a post-intervention survey in the two villages during the next transmission season.  **6.5 Sample sizes**  **6.5.1 Sample size for detection of parasite positive individuals during the dry season:**  The prevalence of sub-patent parasitemia during the dry season is expected to be about 15%. Therefore, the whole two villages will be screened during the dry season for detection of all positives including microscopical cases and subpatent parasitaemia to give the sample size needed for treatment trial.  **6.5.2 Sample size for evaluation of the efficacy of the two combinations**  A trial with 55 subjects on each arm would have 90% power (using a significance level of 0.05) to detect a difference between treatment groups if gametocyte prevalence detected by RT-PCR after treatment is 20% or more on day 3 in AS/SP combination and 5% or less in AS/SP + PQ, allowing for 10% loss to follow up. From earlier surveys the prevalence of sub-patent parasitaemia in the dry season was expected to be about 15% therefore 650 residents of all age groups had to be screened |
|  |
| **6.5.3 Sample size for detection of the impact of treatment on malaria morbidity and mortality**  Based on the previous records the prevalence in the two villages is expected to be around 10%. Therefore, 216 residents from each village, out of the total of 500, will be examined to detect prevalence between 5 - 15 % at 5% level of significance with a design effect of 2.  The sample sizes were calculated using Epi-Info 2002 computer programme.  6.6. Sampling technique and randomization  Persons who were positive by PCR in the dry season will be enrolled in the study for measuring the efficacy of each combination. The list of eligible participants will be sorted according to village and age, to achieve an implicit stratification. The allocations for this ordered list will be generated using restricted randomization with a block size of 12 in Stata version 7 (Statacorp, Texas)  Simple random sampling technique will be used for the selection of the sample size needed for detecting the impact of the treatment on malaria morbidity.  6.7. Data Collection methods, instruments used, measurements  6.7.1.Describe the instruments used for data collection (questionnaire,observation recording form, etc..), studied variables included in these instruments, and methods used to test for the validity and reliability of the instrument.   - Clinical data will be collected by a medical doctor using a questionnaire. - Thin and thick blood films will be collected on slides by finger brick - A parallel drop of blood will be collected on filter paper from the same finger brick for screening by conventional nested PCR technique. - Microvet tubes will be used to collect 150 ul of blood by finger brick from PCR positive individuals only. Samples will be used for detection of subpatent gametocytes by RT-PCR.     6.7.2.Techniques used should be briefly described and referenced  Thin and thick blood films will be stained and used for species identification and parasite density estimation13.  **Detection of low level *P. falciparum* infection during the dry season**  *P. falciparum* DNA will be extracted from filter papers of microscopically negative blood samples14.  Nested PCR will then be used to detect low level *P. falciparum* infections that prevail during the dry season15. Principal genes to be detected are *Pfs*25 and *Pfg*377, which encode gametocyte specific proteins. Results will then be visualized using gel electrophoresis. Detection of gametocytes using RT-PCR RT-PCR method will be used for detection of sub-patent gametocytemia during the dry season16, 17. Briefly, blood samples collected for RNA isolation and RT-PCR of *Pfs25* and *Pfg377* will first be left at room temperature for 30 minutes, to allow exflagellation and microgamete formation. The plasma and the buffy coat will be removed and the red blood cells stored at -70°C. Total RNA will be isolated using RNA isolation kits. RT-PCR of RNA will then be carried out.   - - 1. **Study definitions (eg case definition) should be mentioned.**   Clinical malaria includes those with microscopically diagnosed *P. falciparum* and clinical symptoms.  Sub-patent parasitaemia includes those detected positive by PCR  Gametocyte reservoirs include those detected positive by the RT-PCR.  **6.8.Data Management and Statistical Analysis**  (Describe the overall plan and tests used for data analysis and statistical package used)  The efficiency of the two treatment regimens will be assessed by comparing the proportions detected positive for asymptomatic infections before and after treatment. Comparison will be done using chi-square test and the significance of the results will be measured by the *P-value*.  Malaria prevalence and percent of mortality will be determined from data collected during the transmission season survey. They will be used for evaluation of the intervention by comparing them between the two villages and with data of the previous transmission season for every village. Comparison will also be done by chi-square test.  The data will be analyzed using SPSS (Statistical Package for Social Science) version 10. |

| 1. Implications of study results on disease control    1. Expected results and potential contribution of the project to the relevant control programme   It is expected that by the end of this study the suitable and highly effective combination therapy of antimalarial drugs will be identified. The strategy of treating sub-patent parasiaetimia and gametocyte carriage during the dry season is expected to have great impact in malaria morbidity and mortality in the intervention villages during the transmission season. If the expected results are achieved, this strategy of treatment during the dry season with the identified drugs will be recommended to be incorporated into the national malaria control programme of the Ministry of Health for controlling malaria epidemics in areas of marked seasonal transmission.   - 1. Mechanisms to ensure implementation of research results in the health policy of the concerned control programme of the Ministry of Health - A community physician from Malaria, Schistosomiasis and Leishmaniasis Control programme, Federal Ministry of Health(Deputy Director),is co-investigator in the project. He will be in close contact with the progress of the project and its activities and will be aware by the results. - Copies of the progress reports and the final report will be sent to the Control Prgramme. - Formal meeting can be arranged with the staff of the control programme to discuss the findings of the project and the possibility of implementing them. |
| --- |
| 1. Areas of Integration of Research Activities (if applicable)   The project integrates very well with the activities of a national malaria project (SUD 06/21) receiving TC support from the International Atomic Energy Agency (IAEA). This project will benefit from its field and laboratory facilities. [name] [name], U. of Edinburgh, will supervise the RT-PCR part and we will use the field station in Gadarief rent to his MRC malaria project in the area. [name], Medical statistician in the MRC laboratories in the Gambia, greatly helped in the design and will help in statistical analysis and publication of the work. |

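### Protocol 6.4 and 6.5.1 put microscopy-positive cases into the randomised trial, but 6.6 enrols only PCR-positives and PCR is run only on film-negatives, so the trial population is stated in two incompatible ways

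*Protocol*

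**What the plan says.** **Sections that include film-positives.** Protocol 6.4: "A treatment trial will then be carried out on malaria cases and asymptomatic carriers at the end of the dry season". Protocol 6.5.1 says that both villages are screened "for detection of all positives including microscopical cases and subpatent parasitaemia to give the sample size needed for treatment trial". The study definitions in section 6.7 tie a malaria case to the blood film: "Clinical malaria includes those with microscopically diagnosed" *P. falciparum*, together with symptoms.

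**Section that sets enrolment.** Protocol 6.6: "Persons who were positive by PCR in the dry season will be enrolled in the study for measuring the efficacy of each combination". The eligible list is sorted by village and age and allocated in blocks of 12.

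**Laboratory pathway.** Protocol 6.4: "Samples detected negatives by blood films will be screened by conventional nested PCR". Section 6.7.2 likewise limits DNA extraction to film-negative samples. Section 6.7.1 takes the filter-paper drop from the same finger prick as the film, with no limit by film result, but draws the RT-PCR tube "from PCR positive individuals only".

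**Follow-up and endpoint.** Section 6.4 follows those treated on days 3, 7 and 14 for sub-patent parasitaemia and gametocyte carriage. Section 6.5.2 sizes the comparison on day-3 gametocyte prevalence by RT-PCR, 20% against 5%, with 55 per arm.

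**The concern.** Two sections admit people detected by microscopy. The enrolment rule and the laboratory pathway leave them out. Field staff cannot follow both, and who is randomised is a matter for the protocol itself.

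If 6.4 is followed, three problems arise:

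- Film-positives would be randomised with no molecular baseline. The before-and-after comparison in 6.8 would have no PCR or RT-PCR starting value for them, and 6.8 is in any case worded for asymptomatic infections.
- The day-3 comparison would combine two kinds of infection. The Background (section 4) expects gametocyte density to rise at first after treatment of a malaria attack if the drug has no direct effect on gametocytes, and expects no such wave in treated asymptomatic people. Day 3 falls in the early period where that contrast matters.
- The list is ordered only by village and age, so film status could differ between arms by chance.

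If 6.6 is followed, these problems do not arise, but 6.4 and 6.5.1 then describe a trial that is not the one being run.

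**Working it through.** The point concerns population and sampling, so the main check sets the sections side by side.

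| Step | Film-positive person | Film-negative, PCR-positive person |
|---|---|---|
| In the treatment trial (6.4) | yes, as a malaria case | yes, as a carrier |
| Counted toward the trial sample (6.5.1) | yes | yes |
| Filter-paper drop taken (6.7.1) | yes, no limit stated | yes |
| Nested PCR run (6.4, 6.7.2) | no | yes |
| Meets the enrolment rule (6.6) | no, has no PCR result | yes |
| Baseline RT-PCR tube (6.7.1) | no | yes |
| Follow-up visits (6.4) | yes, if treated in the trial | yes |
| Follow-up RT-PCR tube (6.7.1) | unclear | yes |

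The second column contradicts itself between its first two rows and its fifth. The third column is consistent throughout.

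**Which population do the other sections assume?** Objectives 5.2 look for gametocyte carriers among those with sub-patent infection. Section 6.8 speaks of asymptomatic infections. Section 6.5.2 derives its screening number from the 15% sub-patent prevalence alone:

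- 650 × 0.15 = 97.5 carriers.
- The planned total is 2 × 55 = 110, which would need 110 / 0.15 = 733.3, so 734 people screened.

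The 650 is thus somewhat short of 110, but it rests only on sub-patent carriers, in line with 6.6 and not with 6.5.1.

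**Does dropping film-positives leave too few people?** Section 6.5.3 mentions a total of 500 residents. I read this as per village, because 650 could not be screened from 500 in all. Then 2 × 500 × 0.15 = 150 carriers before exclusions and refusals, against 110 needed. No shortfall follows.

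**The plan's own sample size.** With p1 = 0.20, p2 = 0.05, mean 0.125, two-sided 0.05 and 90% power:

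n = [1.960 × √(2 × 0.125 × 0.875) + 1.282 × √(0.16 + 0.0475)]² / 0.15² ≈ 100.1, so 101 per arm, and 101 / 0.9 = 112.2, so 113 with 10% loss.

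The stated 55 is not reproduced. That is a separate matter and neither supports nor weakens this point.

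**The case against.** The best reply is that 6.6 is the operative enrolment rule. If it is applied, nobody is randomised because of a positive film, and the missing baseline never occurs. Sections 5.2, 6.5.2 and 6.8 agree with 6.6, so 6.4 and 6.5.1 may simply be loose drafting. This largely stands as a guess at intent, and it is why the fix below follows 6.6. It does not remove the contradiction: 6.5.1 plainly counts "all positives including microscopical cases and subpatent parasitaemia to give the sample size needed for treatment trial".

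It can also be said that randomisation protects the comparison between arms even in a mixed population. That is right. What suffers is the definition of the population, the molecular baseline, and the fit of the assumed 20% and 5% to those enrolled.

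Several stronger readings are tempting, but the protocol does not support them:

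- **Film-positives would have no sample at all.** They have a film with a density estimate and, on the text of 6.7.1, a filter-paper drop. Section 6.4 also follows everyone treated. What is missing is a planned baseline PCR or RT-PCR result; follow-up RT-PCR is unclear, not excluded.
- **A malaria case can never be on the PCR-positive list.** The timetable puts the dry-season survey in month 3, a pre-transmission survey in month 7 and treatment in months 7 to 9. A person film-negative and PCR-positive in month 3 could be a malaria case by month 7. This is a possible reading of 6.4, though not a stated one, and it does not rescue 6.5.1.
- **The primary endpoint is lost.** The protocol names no primary endpoint. Day-3 RT-PCR gametocyte prevalence is the endpoint used for sizing.
- **A known share of the trial is affected.** If 1% to 3% of 1,000 residents were film-positive (an assumption), 10 to 30 people would be involved. That is 10/110 = 9% to 30/110 = 27% if the total is fixed at 110, but 10/160 = 6% to 30/180 = 17% if they are added to 150 carriers. Neither the prevalence nor the cap is in the protocol.

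**Conclusion.** The contradiction is real: 6.4 and 6.5.1 include microscopy-positive cases, and 6.6 with the PCR pathway excludes them. The consequences are conditional. Only if film-positives are randomised under 6.4 do they lack a planned baseline PCR or RT-PCR result, have uncertain follow-up RT-PCR, and mix infections in the day-3 comparison.

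The Background's contrast is between a malaria attack and asymptomatic infection, and depends on the drug having no direct effect on gametocytes. It therefore bears most directly on symptomatic film-positives and gives no size for the difference. A reader might infer a shortfall in numbers or a quantified loss; neither is shown. The size of the effect cannot be given, because no dry-season microscopy prevalence is stated.

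The sections should be aligned before randomisation, since RNA not collected at baseline cannot be obtained afterwards.

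**What to change.** Reconcile 6.4, 6.5.1, 6.6 and 6.7.1. The simplest version, consistent with 5.2, 6.5.2, 6.6 and 6.8:

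- Define the randomised efficacy comparison as film-negative, PCR-positive people.
- Report microscopy-positives separately and do not count them toward the 110. This concerns enrolment and analysis only, not how they are managed clinically.

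If the sponsor does intend to randomise microscopy-positives, 6.6 must state that a positive film qualifies. Section 6.7.1 must then extend the RT-PCR tube to them at baseline and at follow-up. In either case, 6.7.1 should say whether its limit to PCR-positives applies only at baseline.

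The first version costs wording only. The second adds RT-PCR assays for each film-positive person enrolled, a number the protocol does not allow one to state.

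### Section 6.5.2 claims 90% power for 55 per arm, but its own inputs give about 62%

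*Protocol*

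**What the plan says.** Section 6.5.2 sizes the randomised comparison of the two combinations in two sentences. The first is the power claim: "A trial with 55 subjects on each arm would have 90% power (using a significance level of 0.05"). Its conditions are "20% or more on day 3 in AS/SP combination and 5% or less in AS/SP + PQ, allowing for 10% loss to follow up". The second takes a 15% dry-season prevalence of sub-patent parasitaemia and arrives at 650 residents to be screened.

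Three other places bear on it:
- Section 6.5.1 says that "the whole two villages will be screened during the dry season for detection of all positives", microscopy-positive cases included.
- Section 6.6 enrols the people found PCR-positive and randomises the ordered list of eligible participants in blocks of 12. It gives no maximum.
- Section 6.8 names the chi-square test. Section 6.5.3 says that the sample sizes came from Epi-Info 2002.

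Whether the 0.05 is one-sided or two-sided is not stated.

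**The concern.** A fall from 20% to 5% is large, but both rates are low, and 50 people per arm means expecting about 10 positives against 2 or 3. That is thin for 90% power. Everything needed to check the claim, apart from sidedness, stands in the sentence itself.

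This is the protocol's only individually randomised comparison. It carries the aim of identifying the appropriate drug (section 5.1), and the section on implications for disease control says that the result is to be recommended to the national malaria control programme. If the stated power is too high, a non-significant difference could be given more weight as evidence that primaquine adds little than the data can bear.

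**Working it through.** **Inputs, all from section 6.5.2 unless noted**
- 55 per arm, equal arms.
- p1 = 0.20 and p2 = 0.05. The text says 20% or more and 5% or less, so this pair is the boundary at which the claim has to hold.
- Significance level 0.05, taken as two-sided (assumption); one-sided is also tried.
- Loss of 10%: 55 × 0.9 = 49.5, about 50 evaluable per arm.
- Chi-square test (section 6.8).

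**Attempt to reproduce the stated 90%**

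Pooled proportion: (0.20 + 0.05)/2 = 0.125. Null variance term: 2 × 0.125 × 0.875 = 0.21875. Alternative variance term: 0.20 × 0.80 + 0.05 × 0.95 = 0.2075.

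Power = Φ{[0.15 − 1.96 × √(0.21875/n)] / √(0.2075/n)}

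At n = 50: [0.15 − 1.96 × 0.0661] / 0.0644 = 0.316, and Φ(0.316) = 0.62.

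The 90% is not reproduced. Other conventions at the same rates:

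| Convention | about 50 evaluable per arm | all 55 evaluable |
|---|---|---|
| Two-sided, standard formula | 62% | 67% |
| Two-sided, unpooled variance | 64% | 69% |
| Two-sided, arcsine | 66% | 70% |
| Two-sided, exact uncorrected chi-square | 66% | 69% |
| Two-sided, Fisher (exact) | 51% | 57% |
| One-sided, standard formula | 74% | 77% |
| One-sided, arcsine | 77% | 80% |

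The most favourable cell combines a one-sided test, the arcsine approximation and no loss at all. It is still 10 points short.

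**Number needed for 90%**

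n = [1.96 × √0.21875 + 1.2816 × √0.2075]² / 0.15² = (0.9167 + 0.5838)² / 0.0225 = 100.1 evaluable per arm.

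Allowing for 10% loss: 100.1/0.9 = 111.2, so about 112 enrolled per arm (113 if 100.1 is first rounded up to 101). The planned 55 is about half of that. With continuity correction the need is 113 to 114 evaluable per arm. One-sided, it is 82 evaluable and 92 enrolled.

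**Effect that 50 evaluable per arm can detect with 90% power**

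About 29% against 5%, or 20% against about 0.5% (two-sided, standard formula).

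**Screening figure in the same section**

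650 × 0.15 = 97.5, about 98 positives. That is below 2 × 55 = 110. Split evenly and less 10%: 98/2 × 0.9 = 44 evaluable per arm, for which the formula gives about 57%. To yield 110 positives at 15%, 110/0.15 = 733 residents would have to be screened, before any exclusions.

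**The case against.** *The rates are given as bounds, so larger effects are covered.* They are, but a power statement over a range has to be true at its edge, and the edge is 20% against 5%. This does not rescue the figure.

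*Sidedness and formula are not stated.* True, and the table allows for it. No choice reaches 90%.

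*The trial need not stop at 110.* This stands. A reader might infer from 6.5.2 that enrolment closes at 55 per arm, and so that the trial will in fact have 62% power. The documents do not say so: 6.5.1 screens both villages completely, and 6.6 enrols the PCR-positive people with no upper limit. The number achieved may be above or below 110, and the documents do not fix it. Section 6.5.3 mentions a total of 500, which could be read per village or overall. The 15% refers to sub-patent parasitaemia only, while microscopy-positive cases would add to the pool and exclusions would reduce it.

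*How the error arose.* With 110 per arm, 10% loss leaves 99 evaluable and about 90% power, so a reader might infer that a per-arm number was taken for a total. Nothing in the protocol confirms this, and the finding does not need it.

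**Conclusion.** The power statement in 6.5.2 is wrong as written. At 20% against 5% with about 50 evaluable per arm, power is about 62% rather than 90%, a gap of some 28 percentage points. This assumes a two-sided 0.05 and that 55 is the number enrolled before loss; relaxing either or both leaves power at 80% or less.

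The consequence is conditional. If 55 per arm are enrolled, the chance of missing the stated effect is close to 4 in 10 (1 − 0.62 = 0.38). What is established is a false claim for 55 per arm, together with a screening number that does not supply even 55 per arm. It is not established that the trial will end with that power, since 6.6 sets no cap.

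**What to change.** 1. Restate the power sentence in 6.5.2: 55 per arm (about 50 evaluable) gives about 62% power, two-sided 0.05, for 20% against 5%; 90% power would need about 100 evaluable (about 112 enrolled) per arm.
2. In the same section, correct the figure of 650 screened, which at 15% yields about 98 positives, and reconcile it with the complete screening of both villages in 6.5.1.
3. Confirm that, as 6.6 already reads, every eligible positive is randomised and that 110 is not a ceiling.
4. Report the power for the number actually enrolled.

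These are wording changes. The downside is only a less favourable stated power; the screening is already planned.

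### Screening 650 residents at 15% prevalence yields about 98 subjects, not the 110 that Section 6.5.2 needs, and 650 contradicts the whole-village screening in Section 6.5.1

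*Protocol*

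**What the plan says.** Protocol Section 6.5.2 sets the size of the drug comparison: "A trial with 55 subjects on each arm would have 90% power (using a significance level of 0.05) to detect a difference", for day 3 gametocyte prevalence of "20% or more on day 3 in AS/SP combination and 5% or less in AS/SP + PQ", "allowing for 10% loss to follow up". The 55 per arm is therefore the number to enrol, not the number left at follow-up. The same paragraph then turns this into a screening target: sub-patent prevalence in the dry season "was expected to be about 15% therefore 650 residents of all age groups had to be screened".

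Four other sections bear on that number:

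- Section 6.5.1 says that "the whole two villages will be screened during the dry season", and counts microscopy cases as well as sub-patent infections among the positives.
- Section 6.2 recruits all residents of both villages but keeps some out of drug testing: pregnant women, "children < 3 year old", people allergic to sulpha drugs, and those with non-falciparum infections. It gives no rates.
- Section 6.5.3 takes "216 residents from each village, out of the total of 500" for the later morbidity survey.
- Section 6.4 puts people with malaria as well as symptom-free carriers into the treatment trial, whereas Section 6.6 enrols those positive by PCR. Under Section 6.4, PCR is run only on samples that are negative on the blood film.

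**The concern.** The word linking prevalence to 650 presents the number as a result of the calculation. Multiplying it back gives fewer subjects than the paragraph has just asked for, even if every positive person is eligible and agrees to take part. The 650 covers all ages, so it also includes people whom Section 6.2 then bars from the drug comparison.

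The adjacent section gives a different instruction, to screen everyone. A field team could work to either. If it worked to 650, the trial would probably enrol fewer than its stated arms. If it worked to Section 6.5.1, the number in 6.5.2 would serve no purpose.

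**Working it through.** **Inputs.** From Section 6.5.2: 55 per arm (110 in total, 10% loss included), 20% against 5%, significance level 0.05, power 90%, prevalence about 15%, and 650 screened. From Section 6.5.3: 216 per village, a total of 500, expected prevalence 10% within 5 to 15%, and design effect 2. Sidedness is not stated; two-sided is used below. The protocol gives no exclusion rates, so those below are assumed.

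**1. Trying to reproduce 650.** Screening number = subjects to enrol / prevalence.
- Enrolled number: 110/0.15 = 733.3, so 734. The stated 650 is not reproduced.
- Number left after loss: 110 x 0.9 = 99, and 99/0.15 = 660. This is close to 650, so the loss allowance was probably left out at this step. Loss to follow-up happens after enrolment, so 110 is the number that screening must supply.

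**2. Yield of 650.**
- 650 x 0.15 = 97.5, or 48.75 per arm. The shortfall is 110 - 97.5 = 12.5, which is 11% of 110.
- Prevalence needed for 650 to give 110: 110/650 = 16.9%.
- Binomial chance of at least 110 positives among 650 at 15%: about 9.5%.

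**3. Exclusions (assumed share of positives who are ineligible).**

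| Ineligible | Yield of 650 | Screened to reach 110 | Yield of 1,000 |
|---|---|---|---|
| 0% | 97.5 | 734 | 150 |
| 5% | 92.6 | 772 | 142.5 |
| 10% | 87.8 | 815 | 135 |
| 20% | 78.0 | 917 | 120 |

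**4. Is 500 per village?** For 10% prevalence with a margin of 5 points, n0 = 1.96² x 0.1 x 0.9 / 0.05² = 138.3. With a finite population of 500, n = 138.3/(1 + 138.3/500) = 108.3, and twice that is 216.7, which matches 216. A population of 250 gives 178 and one of 1,000 gives 243. The per-village sample was thus calculated with a population of 500, which supports 500 per village and about 1,000 in all.

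**5. Effect on power.** Two-sided comparison of 20% with 5%, n evaluable per arm, mean proportion 0.125:

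power = Φ{[0.15 - 1.96 x √(2 x 0.125 x 0.875/n)] / √((0.2 x 0.8 + 0.05 x 0.95)/n)}

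- 55 per arm less 10%, n = 49.5: (0.15 - 0.1303)/0.0647 = 0.304, power about 62%.
- 650 screened, 48.75 per arm less 10%, n = 43.9: (0.15 - 0.1384)/0.0688 = 0.169, power about 57%.

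The screening number therefore accounts for about 5 points. For comparison, 90% power needs 101 evaluable per arm, or 113 enrolled with 10% loss, so the step from 90% to 62% lies in the 55 per arm itself.

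**The case against.** The strongest reply is that nothing in the protocol says screening stops at 650. Section 6.2 recruits every resident and Section 6.5.1 screens both villages to supply the treatment trial, so 650 can be read as a minimum. Screening about 1,000 people at 15% gives about 150 sub-patent positives, comfortably above 110. This stands, and it limits the harm. It does not rescue the number: as a minimum, 650 is still too low for 110.

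A second reply is that 97.5 counts sub-patent infections only, while Sections 6.4 and 6.5.1 bring in microscopy cases. An extra 2% patent prevalence (assumed) would give 650 x 0.17 = 110.5 before exclusions, or about 108.5 if the 15% applies only to film-negative residents. This stands in part. Section 6.6 enrols PCR positives, and 6.5.2 derives 650 from sub-patent prevalence alone, so the protocol does not settle the matter. Prevalence is also only approximate.

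A reader might go further and infer three things that the documents do not support:

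- *That the screening number takes power from 90% to 57%.* It does not. Power is already about 62% with the full 55 per arm after loss.
- *That the trial will enrol only 49 per arm.* That follows only if screening stops at 650, against Sections 6.2 and 6.5.1.
- *That 500 is the population of both villages together, so that 650 could not be screened and only 75 positives would be found.* The wording allows it, but the 216 per village was calculated with a population of 500, and 650 residents could not come from a total of 500. Both point to 500 per village.

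**Conclusion.** The point holds as an arithmetic error and an internal contradiction. At the stated 15%, 650 residents supply about 98 subjects for a trial that must enrol 110, a shortfall of 11% before exclusions, and the number disagrees with the full screening in Section 6.5.1.

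The consequence is modest: about 5 points of power if the team stopped at 650, and none from this cause if both villages are screened and yield at least 110 eligible subjects. This rests on 15% prevalence, enrolment of sub-patent positives only, 500 residents per village, and a two-sided test at 0.05. The whole-village yields also assume that every resident gives a sample. With 20% of positives ineligible, the expected 120 would fall to 110 at about 92% participation (110/120).

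The larger shortfall, from 90% to about 62%, is a separate matter and is not cured by correcting the screening number.

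**What to change.** In Section 6.5.2, replace the 650 by all residents of both villages, about 1,000 at 500 per village, in line with Section 6.5.1. State the expected yield beside it: about 150 sub-patent positives at 15%, less the Section 6.2 exclusions, for example about 120 if 20% are ineligible (an assumed rate, to be labelled as such). In Section 6.5.3, say explicitly that 500 is the size of each village.

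Reconcile Sections 6.4 and 6.5.1 with Section 6.6 on whether microscopy-positive cases count toward the trial sample, because this changes the expected yield.

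Do not substitute 734 as a minimum that delivers 90% power. It would restore the stated 55 per arm before exclusions, but not the stated power.

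The cost is a protocol wording change. Screening both villages in full is already planned, so this correction adds no fieldwork.
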